### Data collection

The endocrinologists will complete a questionnaire for each patient they consult [see Additional file 1]. The questionnaire will capture various elements of each consultation and comprises 16 questions in three sections: (1) Patient characteristics, (2) Procedures and findings, and (3) Recommendations. The questions have been developed based on the results of two previous studies: observing conventional face-to-face diabetes consultations, [19] and process analysis of video teleconsultation for diabetes [20]. The questionnaire has been pilot tested in four consultations and modifications are made to the questions as suggested by the endocrinologists and the researchers. The participants in the telemedicine group will also be asked to complete a patient questionnaire after their video consultation. This satisfaction questionnaire comprised 17 questions in five-point Likert-type scale asking for various aspects of videoconference session.

### Statistical methods

Demographic and baseline data will be reported as absolute numbers, percentage, and/or mean +/− SD. Percentage agreement and the weighted kappa statistic (Kw) will be used to assess inter-rater reliability between the two groups on the agreement on assessments and recommendations made by the endocrinologists [21].

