**Methods/Design:**

A total of 160 people with diabetes will be randomised into either a Telemedicine or a Reference group. Participants in the Reference group will receive two sequential face-to-face consultations whereas in the Telemedicine group one consultation will be conducted face-to-face and the other via videoconference. The primary outcome measure will be a change in the patient’s medication. Secondary outcome measures will be findings in physical examination, detecting complications, and patient satisfaction. A difference of less than 20% in the aggregated level of agreement between the two study groups will be used to identify if videoconference is non-inferior to traditional mode of clinical care (face-to-face).

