### Sample size

This study will evaluate if agreement on the recommendations for the Telemedicine group is not inferior to agreement in the Reference group by more than an acceptable amount. This clinically acceptable amount of variation for diabetes consultation was set as 20% by a group of expert specialist consultants who had more than five years of telemedicine experience. The sample size is calculated based on the incidence rates of 25, 50, 25% for major change, minor change, and no change respectively in the patient medication made by the endocrinologists (significance level 5%, power 80%). It will be possible with a total of 160 participants (80 per each group) to detect any statistically significant difference for the true kappa of 0.7 and the null kappa of 0.5.

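### The 20% margin is set on level of agreement, but two agreement measures are planned without saying which carries it, and the sample size rests on a kappa contrast not tied to it.

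*Protocol article*

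**What the plan says.** Four places in the protocol article bear on this.

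- **Abstract, Methods/Design.** The decision rule is "A difference of less than 20% in the aggregated level of agreement between the two study groups will be used to identify" non-inferiority of videoconference.
- **Outcome measures.** The outcome is the between-group difference in level of agreement. No statistic is named.
- **Statistical methods.** "Percentage agreement and the weighted kappa statistic (Kw) will be used to assess inter-rater reliability between the two groups". No weights are given, and neither measure is named as the one that decides.
- **Sample size.** "This clinically acceptable amount of variation for diabetes consultation was set as 20% by a group of expert specialist consultants". No scale is named. The calculation then assumes "incidence rates of 25, 50, 25% for major change, minor change, and no change respectively", with 5% significance and 80% power, and says that 80 per group suffices "for the true kappa of 0.7 and the null kappa of 0.5". Nothing says that this 0.20 gap in kappa is the 20% margin, or how one converts to the other.

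**The concern.** A non-inferiority claim needs one margin on one measure, and a sample size computed for that comparison. Here the margin is on level of agreement, two statistics could each be meant by that phrase, and the sample size uses a third element: a kappa contrast that looks like the margin because 0.20 and 20% share a digit. A loss of 0.20 in kappa and a loss of 20 points of agreement are in general different amounts.

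Two things are at stake. The quoted power may belong to a different question from the one the trial will answer. And if both statistics were judged against a limit of 0.20, the result could depend on which one is put forward once the data are known.

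**Working it through.** **Inputs.** From Sample size: category rates 0.25/0.50/0.25, kappa 0.7 and 0.5, 80 per group, 5% significance (sidedness not stated), 80% power. From the abstract: 20%, read here as absolute percentage points, which is an assumption.

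**1. The plan's own figure.** For a one-sample test of unweighted kappa against a fixed null, N = [(z_α·τ0 + z_β·τ1)/(κ1 − κ0)]², where τ² is the largest large-sample variance that the stated rates allow: τ0² = 0.5775 at kappa 0.5 and τ1² = 0.4017 at kappa 0.7.

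- One-sided 5%: [(1.645 × 0.760 + 0.842 × 0.634)/0.20]² = 79.5, so 80. The stated figure is reproduced.
- Two-sided 5%: 102.3, so 103. It is not reproduced.

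This is a test of one group against a fixed value, not a comparison of two groups. The match does not prove that unweighted kappa was used. With weighted kappa the same one-sided formula gives anything from 67.1 to 119.5 (linear) or 52.3 to 205.1 (quadratic), depending on the disagreement pattern.

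**2. Conversion for unweighted kappa.** Chance agreement is Pe = 0.25² + 0.50² + 0.25² = 0.375, and Po = Pe + κ(1 − Pe).

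- κ = 0.7: Po = 0.375 + 0.7 × 0.625 = 81.25%.
- κ = 0.5: Po = 0.375 + 0.5 × 0.625 = 68.75%.
- A kappa gap of 0.20 is therefore 12.5 points.
- A loss of 20 points is 0.20/0.625 = 0.32 in kappa (0.70 to 0.38).

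**3. Conversion for weighted kappa.** By chance, adjacent categories are chosen with probability 0.50 and the extremes (Major against No change) with probability 0.125. Expected weighted disagreement is 0.50 × 0.5 + 0.125 = 0.375 (linear) or 0.50 × 0.25 + 0.125 = 0.25 (quadratic).

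| Disagreements | Linear: 20 points = | Quadratic: 20 points = |
|---|---|---|
| All adjacent | 0.20 × 0.5/0.375 = 0.267 | 0.20 × 0.25/0.25 = 0.20 |
| 25% Major against No change | 0.20 × 0.625/0.375 = 0.333 | 0.20 × 0.4375/0.25 = 0.350 |

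**4. Power of the stated rule.** For a difference in percentage agreement with 81.25% in both groups and 80 per group, SE = √(2 × 0.8125 × 0.1875/80) = 0.0617 and power = Φ(margin/SE − z_α).

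| Margin | One-sided 5% | One-sided 2.5% |
|---|---|---|
| 20 points | 94% | 90% |
| 16.25 points (20% relative: 0.20 × 81.25) | 84% | 75% |
| 12.5 points | 65% | 53% |

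**5. If 0.20 were also a kappa margin.** This is a hypothetical rule. I simulated 30,000 trials, with 80 per group, equal true agreement of 81.25%, and one-sided 5% confidence limits based on large-sample standard errors. The table shows how often percentage agreement passes at 20 points while kappa fails at 0.20.

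| Disagreement pattern | Unweighted | Linear | Quadratic |
|---|---|---|---|
| As expected by chance | 29% | 33% | 45% |
| Adjacent only | 30% | about 20% | 6% |

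**The case against.** The strongest reply has four parts.

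- **The plan uses weighted kappa, and 0.32 and 12.5 are unweighted figures.** This stands. With quadratic weights and adjacent-only disagreements the two scales coincide, so 20 points cannot be said to equal a kappa loss of 0.32 for the planned statistic.
- **A reader might infer that 0.20 in kappa is a second non-inferiority margin, and that the trial is set up to give opposite verdicts.** The document does not say so. The 20% is attached only to agreement, and the kappa wording fits a one-sample test. The conflict rates in step 5 are conditional on that inference. They also depend on the rule: by point estimates instead of confidence limits, with unweighted kappa, adjacent-only disagreements and no true loss, conflict is only about 2%.
- **The choice of weights and the ranking of supportive statistics usually belong in an analysis plan, which is not shown.** This is fair for the weights taken alone. It does not cover a margin, a pair of measures and a sample size that the article itself states and that do not fit together.
- **Percentage agreement is the more lenient choice.** This is also fair. It is not chance-corrected. If video were truly 12.5 points worse (unweighted kappa 0.50 against 0.70), a 20-point rule would still pass about 30% of the time at one-sided 5%, against about 5% for a kappa rule at 0.20. That is a reason to confirm the margin with the panel, not to leave the measure open.

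**Conclusion.** The concern holds in this form: the measure that carries the 20% is not fixed, and the stated sample size and 80% power are not for the stated between-group criterion. For that criterion, read as 20 absolute points of agreement, power is about 94% (one-sided 5%) or 90% (one-sided 2.5%), so 80 per group is enough. If the panel meant 0.20 in kappa, the unweighted equivalent is 12.5 points and power falls to about 65% or 53%. These figures assume the protocol's category rates, 81.25% agreement in both groups and no dropout.

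Two stronger readings are not supported: that 20 points is a fixed kappa loss of 0.32, and that a particular share of trials will give contradictory results. The first is true only of unweighted kappa. The second needs a kappa margin that the protocol never states, and even then the share runs from about 6% to 45%.

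**What to change.** - Name the between-group difference in percentage agreement as the single deciding measure, with an absolute margin of 20 percentage points judged by a confidence limit at a stated one-sided level. This follows the abstract.
- Report weighted kappa per group with stated weights and a confidence interval, as supportive only and with no non-inferiority claim.
- Ask the expert panel to confirm that 20% meant absolute points of agreement.
- Replace the kappa contrast in Sample size with the power for that comparison, using the step 4 figures.
- If the panel meant 0.20 in kappa, state the margin on the kappa scale with its weights and restate power for it.
- Label any conversion between points and kappa as unweighted.

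The cost is a wording change in Statistical methods and Sample size and one query to the panel. The stated power figure changes, and the deciding measure is not chance-corrected, which is why kappa should still be reported. If the panel meant the kappa scale, the shortfall in power would have to be acknowledged or the sample size reconsidered.

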### Sample size

This study will evaluate if agreement on the recommendations for the Telemedicine group is not inferior to agreement in the Reference group by more than an acceptable amount. This clinically acceptable amount of variation for diabetes consultation was set as 20% by a group of expert specialist consultants who had more than five years of telemedicine experience. The sample size is calculated based on the incidence rates of 25, 50, 25% for major change, minor change, and no change respectively in the patient medication made by the endocrinologists (significance level 5%, power 80%). It will be possible with a total of 160 participants (80 per each group) to detect any statistically significant difference for the true kappa of 0.7 and the null kappa of 0.5.

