### Aims and objectives

In this study we are seeking to identify if telemedicine is a reliable vehicle for providing specialty consultation for people with diabetes using videoconferencing, with the implication that it would be useful to utilise when usual care is either not available or difficult to deliver. The aim of the study is to test the level of clinical agreement achieved using specialist to patient videoconferencing (VC) compared with face-to-face (FTF) consultation. To place this level of agreement in context, it will also establish the level of agreement among specialists using face-to-face consultation. This approach enables the variation in clinical decision making among clinicians to be identified, and thus to be differentiated from the effect of the VC mode of service delivery.

This study will test the hypothesis that the clinical assessment and recommendations as determined by an alteration in medication type or dose made by endocrinologists for people with diabetes via videoconference are significantly different from those made through face-to-face consultation (null hypothesis). Secondary hypotheses will apply the same analytic techniques to the other aspects of diabetes consultation: (i) ordering lab tests or other diagnostic intervention; (ii) initiation of new medication(s) or dose adjustment of the previously prescribed drugs for dyslipidaemia and/or hypertension; (iii) detection or management of diabetes related complications; and (iv) referring to other specialists or arranging hospital admission.

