## Methods/design

This study is a repeated-measure non-inferiority randomized controlled trial. All patients participating in the study will receive two consultations (one original consultation and one additional consultation; called paired-consultation in this paper) by two different endocrinologists. Level of agreement between the recommendations made via VC versus FTF for the same patient by two endocrinologists will be calculated. This constitutes VC-FTF paired-consultations. Since there is likely to be a certain level of clinical variability between clinicians, the level of agreement in VC-FTF paired-consultations will then be compared against the level of agreement between two endocrinologists when they consult a patient in standard clinical practice (FTF-FTF). This arrangement will determine whether any lack of agreement is likely to be a result of the videoconference modality, or just normal variation between doctors.

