### Outcome measures

The outcome measure of this study is the difference in level of agreement between the two groups. Agreement will be calculated for each group (Reference group: FTF-FTF; Telemedicine group: FTF-VC or VC-FTF) and compared. For the comparison between two consultations to be accurate, it is necessary that the endocrinologists be blinded to each other’s assessment and recommendations. Part of this information can be communicated by the patient, which is inevitable, however the research endocrinologist has been requested to refrain from giving information about the assessment and treatment plan to the patient during the first consultation. Since the research endocrinologist adds nothing to the patient chart (either in hard copy or electronic records), it will ensure that the endocrinologists will be blinded to each other’s opinion on each patient.

The primary outcome measure is the level of change in patient’s medications during the consultation. Based on its impact, medication change is divided into three categories: Major, Minor, and No change (Table 2). When more than one category is applicable to a participant, the highest impact will be regarded as the overall impact of the medication change.

**Table 2 T2:** The categories of the impact of medication change

**Medication**	**Change**	**Category**
Insulin	Initiation of insulin	Major
	Cessation of Insulin	Major
	Change in regimen (type, injection frequency)	Major
	Dose adjustment	Minor
	No change	No change
Other hypoglycaemic agents	Initiation of new drugs	Major
	Cessation of drugs	Major
	Dose adjustment	Minor
	No change	No change
Other medications (hypertension, lipids, etc.)	Initiation of new drugs	Major
	Cessation of drugs	Major
	Dose adjustment	Minor
	No change	No change

Secondary outcomes focus on performing the physical examination, detection of diabetes complications and patient satisfaction. For each video consultation, the endocrinologist will be asked about any technical problem or limitation during the video visit. This will assist in understanding the barriers of videoconferencing for consulting people with diabetes.

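### The stated 80% power fits a test of one kappa against a fixed value; for the planned comparison of two estimated kappas, 80 per group gives about 65% or 53% (unweighted)

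*Protocol article*

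**What the plan says.** The Sample size section sets a two-group non-inferiority aim, namely whether "agreement on the recommendations for the Telemedicine group is not inferior to agreement in the Reference group by more than an acceptable amount", with a 20% margin chosen by an expert panel. It then gives the inputs: "incidence rates of 25, 50, 25% for major change, minor change, and no change respectively", with "significance level 5%, power 80"%. The group size follows from one contrast: "80 per each group) to detect any statistically significant difference for the true kappa of 0.7 and the null kappa of 0.5".

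Other sections describe the comparison in the same two-group way:

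- Methods/design: "the level of agreement in VC-FTF paired-consultations will then be compared against the level of agreement between two endocrinologists" seeing the patient face-to-face.
- Aims and objectives, on the Reference value: "it will also establish the level of agreement among specialists using face-to-face consultation".
- Outcome measures: "The outcome measure of this study is the difference in level of agreement between the two groups".
- Abstract, on the criterion: "A difference of less than 20% in the aggregated level of agreement between the two study groups".

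Statistical methods names percentage agreement and weighted kappa, without giving the weights. The article does not state the sidedness of the 5% level, the kappa used for the sample size, or whether the 20% is on the kappa or the percentage-agreement scale.

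**The concern.** One true kappa set against one null kappa describes a test of a single agreement coefficient against a constant. A null of 0.5 is what remains if a Reference kappa of 0.7 is taken as known and 0.20 is subtracted. In this trial the Reference kappa is not known. It is estimated from the other 80 participants, and its sampling error enters the comparison.

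If that error was left out, the printed power belongs to a different test. In a non-inferiority trial the consequence is specific: a video service that agrees just as well as face-to-face care would fail to be shown non-inferior more often than the planned 20% of the time, and readers could take that failure as evidence against video. The wording about detecting a difference also describes a difference test, not a non-inferiority test.

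**Working it through.** **Inputs from the Sample size section.** Category rates 0.25/0.50/0.25, kappa 0.7 and 0.5, 5%, 80%, 80 per group.

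**Assumptions, because the article is silent.** Sidedness, weights, and how disagreements spread over the 3x3 table. Two patterns are used: *proportional* (disagreements spread as the category rates imply) and *adjacent-only* (no disagreement between major change and no change).

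**Step 1: agreement implied by kappa.** Chance agreement is pe = 0.25² + 0.50² + 0.25² = 0.375. Raw agreement is po = pe + κ(1 − pe), so po = 0.8125 at κ = 0.7 and 0.6875 at κ = 0.5.

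**Step 2: variance per pair.** Large-sample formula: V = [Σ p_ij{w_ij − (w̄_i + w̄_j)(1 − κ)}² − {κ − pe(1 − κ)}²]/(1 − pe)². For weighted kappa, pe is the weighted chance agreement. For unweighted kappa:

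- Proportional: V = 0.540 (SD 0.735) at 0.5, and 0.388 (SD 0.623) at 0.7.
- Adjacent-only: V = 0.5775 at 0.5, and 0.4017 at 0.7.

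**Step 3: reproduce the plan's figure.** One-sample test: n = [(z_α√V0 + z_β√V1)/0.2]².

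- Proportional, one-sided 5%: [(1.645 × 0.735 + 0.842 × 0.623)/0.2]² = about 75. Two-sided: about 96.
- Adjacent-only, one-sided 5%: 79.5, so 80 (power at 80 is 80.2%). Two-sided: about 102.

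So 80 matches the one-sided requirement for **one** group against a fixed value.

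**Step 4: the planned comparison.** Both kappas are estimated from 80, both true values are 0.7 and the margin is 0.20. Power = Φ(0.20/√(2V/80) − z_α). Unweighted, proportional: SE = 0.623 × √(2/80) = 0.0985 and 0.20/0.0985 = 2.03, which gives Φ(2.03 − 1.645) = 65% and Φ(2.03 − 1.96) = 53%.

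| Kappa fixed at 0.7 | Pattern | V | One-sided 5% | One-sided 2.5% |
|---|---|---|---|---|
| Unweighted | proportional | 0.388 | 65% | 53% |
| Unweighted | adjacent-only | 0.402 | 64% | 51% |
| Linear weights | proportional | 0.437 | 61% | 48% |
| Linear weights | adjacent-only | 0.341 | 70% | 58% |
| Quadratic weights | proportional | 0.647 | 47% | 35% |
| Quadratic weights | adjacent-only | 0.273 | 78% | 68% |

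Simulation of 20,000 trials under the proportional pattern gives 65%/53%, 60%/49% and 50%/38% for the three weightings.

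These patterns are not outer limits. Over all tables with the stated category rates, the best case at kappa 0.7 is 71%/59% unweighted, 70%/58% linear and 78%/68% quadratic. The worst is 35%/24% (quadratic). None reaches 80%.

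**Step 5: a higher weighted kappa.** In the adjacent-only table with unweighted kappa 0.7, quadratic kappa is 0.81 with V = 0.181. Power is then 91% (one-sided 5%) or 84% (one-sided 2.5%).

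**Step 6: the percentage-agreement scale.** With a 20-point margin, SE = √(2 × 0.8125 × 0.1875/80) = 0.0617 and 0.20/0.0617 = 3.24, so power is 94% (one-sided 5%) or 90% (one-sided 2.5%). At 68.75% agreement in both groups SE = 0.0733, so power is 86% or 78%. The two margins differ: 20 points is 0.20/0.625 = 0.32 kappa, while 0.20 kappa is 0.8125 − 0.6875 = 12.5 points.

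**The case against.** Three points on the other side have force.

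- **The scale is open.** The abstract speaks of a 20% difference in aggregated agreement, and Statistical methods lists percentage agreement first. On that scale 80 per group is adequate at 81% agreement. A reader might infer that the trial is underpowered outright or must recruit more; the article does not support that. The shortfall is on the kappa scale. It stands there because kappa is the only scale on which the article states its power, and no percentage-agreement calculation is shown.
- **Weighted kappa does not always make things worse.** A reader might infer that moving to the planned weighted kappa lowers the power. That holds under proportional disagreement and reverses under adjacent-only disagreement, which is at least as plausible for an ordered major/minor/no-change scale and is also the pattern that reproduces 80. Only a range is defensible.
- **The method is inferred.** The article does not say that it used a one-sample test or unweighted kappa. The case rests on the single true/null pair and on n coming out at 75 to 80. It should be put as what the inputs fit.

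None of this supplies the missing term for the Reference group. Nor is this detail left to a fuller document: the article prints the inputs, the group size and the power.

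**Conclusion.** The point holds on the kappa scale. The printed inputs fit a one-sample calculation, while the trial compares two estimated agreements. With 80 per group, both true kappas 0.7 and a 0.20 kappa margin, power for unweighted kappa is about 64-65% (one-sided 5%) or 51-53% (one-sided 2.5%). A video service with equal agreement would thus fail in about 35-36% or 47-49% of trials, against the planned 20%. For a weighted kappa of 0.7 the range over the two patterns is 47-78% or 35-68%. Among the weighted cases examined, power passes 80% only where the true weighted kappa is above 0.7, as with quadratic kappa 0.81.

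These figures assume the stated category rates in both consultations, equal true kappas and large-sample variances. Whether 160 participants are enough remains conditional on the scale of the margin, which the article does not fix.

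**What to change.** Keep 160 participants and rewrite the power sentence in the Sample size section:

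1. Delete the wording about detecting a significant difference.
2. State the comparison as non-inferiority of two estimated kappas with a 0.20 margin, and name the sidedness and the weights.
3. Give the power as about 65% (one-sided 5%) or 53% (one-sided 2.5%) for unweighted kappa, and for the weighted kappa in Statistical methods the range 47-78% or 35-68% at a true value of 0.7, with the disagreement pattern assumed.
4. If the panel meant 20 percentage points of raw agreement, say so and give the power on that scale: about 94%/90% (one-sided 5%/2.5%) at 81% agreement and 86%/78% at 69%. Disclose that this margin equals about 0.32 kappa.

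Items 1 to 3 cost only text and a less favourable power figure. Item 4 is more than a change of wording: it gains power by accepting a looser margin than the 0.7 versus 0.5 contrast implies, so it needs confirmation that this is the margin the panel set.
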